### Recruitment procedures

Three strategies are used to recruit participants with FC. The first relies on the participant bank of over 600 patients, built up from prior research team work in functional constipation related studies since 2007. The second relies on referrals from the two study sites (Lee Kee Memorial Dispensary and Li Ka Shing Specialist Clinic of Prince of Wales Hospital) from our co-investigators (Co-Is). The third strategy consists of posted advertisement in local newspapers and a press conference to introduce our research.

All patients diagnosed with functional constipation by the physicians (Co-Is) are referred to the principal investigator (PI) and/or to the research assistants (RA) to determine whether they meet diagnostic criteria of excessive constipation according to TCM theory. There is inconsistency among different TCM practitioners regarding pattern differentiation for FC. If any inconsistency occurs for an individual patient concerning pattern identification, the other senior CMP with more than 20 years clinical practice will be invited to make the diagnosis of TCM pattern independently to ensure the consistence of the diagnosis. The aims, procedures and nature of the study, and possible side effects are explained by the PI and/or the RAs before a written consent form is obtained from each subject who agrees to participate. Moreover, patients are informed that they are free to withdraw at any time during the study. All patients undergo a 2-week, drug-free observation period. Meanwhile, they have to complete a stool and symptom diary to confirm their diagnosis. Blood tests of liver and renal function (blood urea, creatinine, alanine transaminase and aspartate transaminase, alkaline phosphatase and bilirubin), and plain abdominal X-ray for colonic transit study are arranged. Patients are considered eligible for the study if their diaries reflect conformance with the Rome III criteria for a diagnosis of functional constipation, and if they also have normal liver and renal function. Recruited patients will obtain their intervention assignment from the PI and/or RAs.

### Assignment and blinding

Block randomization was carried out in 1:1:1 ratio according to the sequence generated with Random Allocation Software (Version 1.0.0), Isfahan, Iran. The RA assigns treatments according to the codes that are kept in opaque sealed envelopes with consecutive randomization numbers. Treatment assignments will not be revealed and are blinded to the patients and investigators (including statisticians) until the entire study is completed. At the last visit, all patients and the PI/RAs will complete a questionnaire about which treatment (CHM group, WM group or placebo group) the patients received to evaluate the success of blinding. Code breaks should only occur in exceptional circumstances when knowledge of the actual treatment is absolutely essential for further management of the patient.

### Sample size calculation

From the results of the placebo-control study, the response rate of MZRW was 43.3% [14]. Assuming the response rates for TCM, senna and placebo were 40%, 20% and 10%, respectively. Therefore, 82 patients per treatment group were deemed sufficient to achieve 80% power in detecting treatment differences, based on two-sided Chi-square test without continuity correction at a significance level of 0.025 (used to maintain the overall significance level at 5%). Further, assuming a 15% dropout rate, we concluded that a total of 291 patients (97 per arm) would need to be recruited to ensure statistically significant results. The calculation is performed using StudySize 2.0 software, London, UK.

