In the current trial, we seek to evaluate the efficacy and safety of MZRW by comparing it with the commonly used stimulant laxative senna, as well as with a placebo, for patients with FC diagnosed with the TCM excessive syndrome. Senna is a stimulant laxative which facilitates the passage of stools by altering intestinal electrolyte transport and increasing intestinal motor activity [15]. Although no placebo-controlled trials were found, laxatives containing senna and fiber were more efficacious than lactulose [4]. Up to 26% of the patients underwent successful relief of impaction with senna combined with mineral oil [16]. Due to its low cost, safety and ease of ingestion, senna is widely adopted and prescribed in clinical practice. The use of senna remains the first-line treatment for the management of constipation according to the local guidelines of internal medicine published by the Hospital Authority, Hong Kong [17].

The study was financially supported by Food and Health Bureau, Hong Kong, China, through its Health and Health Services Research Fund (project no. 09101501) and was registered with an identifier (NCT01695850) in Clinical Trial.gov. This funding source had no role in the design of this study and will not have any responsibility during its execution, analyses, interpretation of the data, or decision to submit results.

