### Statistical analysis

All efficacy and safety analyses will be conducted according to the intention-to-treat (ITT) principle. Missing values will be imputed by the last-observation-carried-forward method. The statistical analysis will be performed using the Statistical Packages of Social Sciences (SPSS) for Windows version 16.0. The statistical significance is defined as two-sided *P* value of <0.05. Baseline characteristics will be reported as mean (SD). Baseline differences among the groups will be assessed with the use of Student’s t-test for normally distributed continuous variables and the non-parametric Mann-Whitney U test for non-normally distributed variables. For categorical variables, chi-squared test or Fisher’s exact test will be used. Comparisons between groups will be conducted by using an analysis of covariance (ANCOVA) with baseline as covariate. All items and subscales will be compared between groups for each 6-week treatment using ANCOVA, with treatment group as a factor in the model and baseline as the covariate. The changes from baseline to endpoint of treatment in scores will be tested with repeated measure analysis of variance (ANOVA). Within group differences will be assessed with paired t-test for normally distributed data and Wilcoxon signed-rank test for non-normally distributed data.

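### The 80% power stated for unnamed treatment differences does not hold across the three contrasts: at 82 per arm and two-sided 0.025 it is about 99%, 72% and 33%

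*Protocol article*

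**What the plan says.** The Sample size calculation section gives one rate per arm: "Assuming the response rates for TCM, senna and placebo were 40%, 20% and 10%, respectively". From these it infers that "82 patients per treatment group were deemed sufficient to achieve 80% power in detecting treatment differences", based on a "two-sided Chi-square test without continuity correction at a significance level of 0.025", a level "used to maintain the overall significance level at 5" per cent. Allowing for 15% dropout, it arrives at 97 per arm and 291 in total. No pair of arms is attached to the 80%.

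Three other places bear on the point:

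- The Background states the aim as evaluating MZRW against senna and against placebo. Senna versus placebo is not named as a comparison. On earlier evidence for senna it says: "Although no placebo-controlled trials were found, laxatives containing senna and fiber were more efficacious than lactulose".
- Assignment and blinding gives equal allocation: "Block randomization was carried out in 1:1:1 ratio".
- Statistical analysis sets significance at two-sided P below 0.05, not 0.025, and applies intention to treat with last observation carried forward.

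**The concern.** Three assumed rates imply three pairwise differences of very different size: 30, 20 and 10 percentage points. One sample size cannot give the same power for all of them, yet the section attaches a single 80% to plural, unnamed differences. A reader could apply it to any pair.

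The consequence is greatest for senna versus placebo. The article reports finding no placebo-controlled trials of senna, so this trial's placebo arm is the direct check on its active control. If senna is not significantly better than placebo, a reader relying on 80% power could conclude that senna is inactive in these patients. At the plan's own rates, a miss on that contrast is at least about as likely as not, even if senna works exactly as assumed.

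The wording also hides a shortfall in the head-to-head contrast, which the article presents as the trial's new contribution.

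**Working it through.** **Inputs.** Rates 0.40, 0.20 and 0.10; 82 per arm (97 before dropout); two-sided chi-square test without continuity correction at 0.025, all from Sample size calculation. Alternative alpha 0.05 from Statistical analysis. Equal allocation from Assignment and blinding.

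**Formula.** With d = p1 − p2, p̄ = (p1 + p2)/2, s0 = √[2p̄(1 − p̄)] and s1 = √[p1(1 − p1) + p2(1 − p2)]:

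- power = Φ[(d√n − z·s0)/s1], where z = 2.2414 at two-sided 0.025 and 1.9600 at 0.05;
- n for 80% power = [(z·s0 + 0.8416·s1)/d]².

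**Where 82 comes from.** For 40% versus 20%, s0 = √(2 × 0.30 × 0.70) = 0.6481 and s1 = √(0.24 + 0.16) = 0.6325.

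- At 0.05: n = [(1.9600 × 0.6481 + 0.8416 × 0.6325)/0.20]² = 81.2, rounded up to 82. This reproduces the plan's figure.
- At the stated 0.025: n = [(2.2414 × 0.6481 + 0.8416 × 0.6325)/0.20]² = 98.5, rounded up to 99.
- No pair gives 82 at two-sided 0.025: 40% versus 10% needs 39 and 20% versus 10% needs 242.

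The dropout step reproduces: 82/0.85 = 96.5, rounded up to 97, and 3 × 97 = 291.

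**Power at 82 per arm, two-sided 0.025.**

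- MZRW versus placebo: s0 = 0.6124, s1 = 0.5745, d√n = 2.7166. Power = Φ[(2.7166 − 2.2414 × 0.6124)/0.5745] = Φ(2.34) = 99.0%.
- MZRW versus senna: d√n = 0.20 × √82 = 1.8111. Power = Φ[(1.8111 − 2.2414 × 0.6481)/0.6325] = Φ(0.567) = 71.5%.
- Senna versus placebo: s0 = 0.5050, s1 = 0.5000, d√n = 0.9055. Power = Φ[(0.9055 − 2.2414 × 0.5050)/0.5000] = Φ(−0.453) = 32.5%.

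**Exact check.** Summing binomial probabilities over every table in which the uncorrected chi-square test rejects gives:

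| Contrast | 82 per arm, 0.025 | 97 per arm, 0.025 | 82 per arm, 0.05 | 97 per arm, 0.05 |
|---|---|---|---|---|
| MZRW vs placebo (40% vs 10%) | 99.2% | 99.8% | 99.7% | 99.9% |
| MZRW vs senna (40% vs 20%) | 72.3% | 80.1% | 80.7% | 87.0% |
| Senna vs placebo (20% vs 10%) | 32.8% | 38.8% | 43.4% | 50.3% |

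For 80% power, senna versus placebo would need 242 per arm at 0.025 or 199 at 0.05.

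**Joint pattern.** In 400,000 simulated three-arm trials at the assumed rates, MZRW beats senna while senna does not significantly beat placebo in about 55% of trials at 82 per arm and 0.025, and in about 47% at 97 per arm and 0.05. All three differences are significant in about 17% and 40% respectively.

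**The case against.** The strongest reply is that the plan never promised power for senna versus placebo. The aim names only the two MZRW contrasts. A level of 0.025 is 0.05/2, which fits two comparisons; an equal split over three would be 0.0167. This stands. Low power for a contrast that the plan neither names nor powers does not make its sample size wrong.

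A reader might go further and infer that the head-to-head result is uninterpretable unless senna is shown to be active. The documents do not support that. No non-inferiority or equivalence aim is stated, for which proof of an active comparator would be essential. For superiority, MZRW is tested directly against placebo with about 99% power. What remains is caution in describing senna's own effect.

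Nor does the analysis section show that a senna-placebo responder test is planned as confirmatory. Its sentence "Comparisons between groups will be conducted by using an analysis of covariance (ANCOVA) with baseline as covariate" adjusts for baseline and leads into items and subscales, so it concerns scores rather than the binary primary outcome.

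It is also fair that intention to treat with imputation may bring up to 97 per arm into the analysis. That takes MZRW versus senna to about 80% at 0.025, provided the assumed rates hold with imputed outcomes included. But the section claims 80% at 82, and senna versus placebo is still only 39%.

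Finally, details of a supportive comparison can be left to an analysis plan that is not shown. The power sentence itself, however, is in this document.

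**Conclusion.** The point holds as an over-broad power statement. At 82 per arm and two-sided 0.025, the single 80% stands for about 99%, 72% and 33%. MZRW versus senna, very probably the contrast behind the figure of 82, falls about 8 points short at the stated alpha and reaches 80% only at 0.05 or with all 97 per arm analysed. Senna versus placebo falls 30 to 47 points short across both alphas and both sample sizes. Because it was probably never meant to be powered, that second shortfall concerns wording and interpretation rather than a miscalculated sample size.

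These figures rest on the plan's own rates, equal arms and the uncorrected chi-square test. That only two contrasts were intended is an inference from the aim and the alpha split; the section does not say so.

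**What to change.** In Sample size calculation:

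1. Name MZRW versus senna and MZRW versus placebo as the powered contrasts.
2. Choose one alpha for them, reconciling 0.025 here with 0.05 in Statistical analysis, and restate each power at that alpha. At 0.025 this is about 72% and 99% with 82 per arm, or about 80% and above 99% with 97. At 0.05 with 82 per arm it is about 81% and above 99%. Simply attaching the present 80% to MZRW versus senna at 82 per arm and 0.025 would be wrong.
3. State that senna versus placebo is not powered: about 33% at 82 per arm and 39% at 97, at 0.025.

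In Statistical analysis, add that senna versus placebo will be reported as a non-confirmatory risk difference in response rate with a 95% confidence interval, and that a non-significant result will not be read as senna being inactive.

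This costs a few sentences and no extra patients. The downside is a less favourable stated power, and a more guarded description of the active control.

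### 82 per arm gives 80% power for MZRW versus senna at two-sided 0.05; at the stated 0.025 the power is about 72%, and 80% needs 99 per arm

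*Protocol article*

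**What the plan says.** All the inputs are in the Sample size calculation section of the protocol article.

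- Rates: "Assuming the response rates for TCM, senna and placebo were 40%, 20% and 10%, respectively".
- Level: "at a significance level of 0.025 (used to maintain the overall significance level at 5" per cent.
- Result and test: "82 patients per treatment group were deemed sufficient to achieve 80% power in detecting treatment differences, based on two-sided Chi-square test without continuity correction". No pair of arms is named.
- Inflation: "assuming a 15% dropout rate", it concludes that "a total of 291 patients (97 per arm) would need to be recruited".

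The Statistical analysis section then defines significance as a two-sided P value below 0.05 and does not mention 0.025. It specifies intention-to-treat analysis with last observation carried forward (LOCF).

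**The concern.** A level of 0.025 per comparison with an overall 5% reads as a Bonferroni split over two comparisons, presumably MZRW against each control. The harder of the two is MZRW versus senna (40% versus 20%). For that pair, 82 is the familiar answer at two-sided 0.05, which suggests that the split was announced but did not enter the calculation.

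The Abstract and Background present the comparison with conventional western medicine as the gap this trial fills; MZRW had already been compared with placebo. If power for the senna comparison is below the stated 80%, a non-significant result there carries less information than readers will be led to think. The unqualified phrase about treatment differences could also be read as covering senna versus placebo, which this sample size cannot support.

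**Working it through.** **Inputs.** Response rates 0.40, 0.20 and 0.10, uncorrected two-sided chi-square test, level 0.025, power 80%, dropout 15% (Sample size calculation); equal allocation, "Block randomization was carried out in 1:1:1 ratio" (Assignment and blinding).

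**Formula (pooled variance, no continuity correction).**

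n per arm = [z(1−α/2)·√(2p̄(1−p̄)) + z(0.80)·√(p₁(1−p₁)+p₂(1−p₂))]² / (p₁−p₂)²

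For 0.40 versus 0.20: p̄ = 0.30, √(2×0.30×0.70) = 0.6481, √(0.24+0.16) = 0.6325, and z(0.80)×0.6325 = 0.8416×0.6325 = 0.5323.

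**Step 1: reproduce the stated 82.** At two-sided 0.05, 1.9600×0.6481 = 1.2702, so n = (1.2702+0.5323)²/0.04 = 81.2, rounded up to **82**. This is the stated figure.

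**Step 2: apply the stated level.** At two-sided 0.025, 2.2414×0.6481 = 1.4526, so n = (1.4526+0.5323)²/0.04 = 98.5, rounded up to **99**.

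**Step 3: power at 82 per arm.** Power = Φ{[0.20·√n − z(1−α/2)×0.6481]/0.6325}, with 0.20·√82 = 1.8111.

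- At 0.05: Φ[(1.8111−1.2702)/0.6325] = Φ(0.855) = 80.4% (exact enumeration 80.7%).
- At 0.025: Φ[(1.8111−1.4526)/0.6325] = Φ(0.567) = **71.5%** (exact 72.3%).

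**Step 4: does another reading return 82?** At two-sided 0.025 and 80% power:

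| Variant | n per arm |
|---|---|
| 40% vs 20%, unpooled variance | 96 |
| 40% vs 20%, arcsine | 98 |
| 40% vs 20%, continuity-corrected | 109 |
| 43.3% (earlier trial) vs 20% | 75 |
| MZRW vs placebo, 40% vs 10% | 39 |
| Senna vs placebo, 20% vs 10% | 242 |

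A global three-arm chi-square test at 0.025 with 82 per arm has about 98% power. None of these matches. One-sided 0.025 does give 82, being the same calculation as two-sided 0.05, but the text says two-sided.

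**Step 5: dropout.** 82/0.85 = 96.5, so 97 per arm and 3×97 = 291. This step reproduces, so the fault lies in the level alone. The same step from 99 gives 99/0.85 = 116.5, so 117 per arm and 351 in total.

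**Step 6: power by comparison at two-sided 0.025 (normal approximation).**

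| Comparison | 82 per arm | 97 per arm |
|---|---|---|
| MZRW vs senna | 71.5% | 79.3% (exact 80.1%) |
| MZRW vs placebo | 99.0% | 99.7% |
| Senna vs placebo | 32.5% | 38.4% |

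**Step 7: sensitivity case, an assumption not in the protocol.** If all 97 are analysed and the 15% who drop out count as non-responders, the rates become 0.85×0.40 = 0.34 and 0.85×0.20 = 0.17. Power for MZRW versus senna at 0.025 is then 68.6% (exact 69.7%).

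**The case against.** The strongest reply is that the planned analysis is not of 82 per arm. The trial recruits 97 per arm and analyses by intention to treat with LOCF, so dropouts stay in. At 97 per arm and two-sided 0.025, power for MZRW versus senna is 79–80%, essentially the target. MZRW versus placebo keeps about 99% in any case, and the misstated number does not affect type I error. It can also be said that a 0.025 level fits two MZRW comparisons, so the plan never undertook to power senna versus placebo.

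Much of this stands as context. The practical loss may be small, and the non-responder case in step 7 is a sensitivity case, not the protocol's rule. But the article attaches its 80% to 82 patients and treats the other 15 per arm as dropout allowance. Recovering 80% at 97 requires patients who leave early to show the full treatment difference through carried-forward values, which the article does not claim. The senna versus placebo figure is not a second arithmetic error; it shows only that the power statement must name its pairs.

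**Conclusion.** The statement is wrong as written. With the article's own rates, test, level and power, the number per arm is 99, not 82. At 82 evaluable per arm, power for MZRW versus senna is about 72%, a type II error of about 28% instead of 20%. The exact match at two-sided 0.05 indicates that the split was not applied, or was applied per tail; the document does not show which.

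The shortfall is confined to MZRW versus senna. It shrinks to almost nothing only if all 97 per arm are analysed with no dilution of the effect. All figures rest on the assumed 40%, 20% and 10%.

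**What to change.** Keep 291 patients and correct the text before unblinding, in one of two ways.

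1. **Keep the split and restate the power.** At two-sided 0.025, 82 evaluable per arm give about 72% for MZRW versus senna and about 99% for MZRW versus placebo. The 79–80% at 97 per arm can be added with its assumption.
2. **Preferred: change the multiplicity rule.** Test MZRW versus placebo first and, only if it is significant, MZRW versus senna, each at two-sided 0.05, and delete the 0.025 wording. Simulated power for the senna step is about 81% at 82 per arm and 87% at 97, with family-wise error for the two tests held at 5%. The stated 82 and 80% then become correct.

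The cost of option 2 is that no senna claim is possible if the placebo comparison fails; under the assumed rates that happens in fewer than 0.5% of trials. Holm's procedure over the same two comparisons has almost the same power for MZRW versus senna (80.6% at 82 per arm in simulation) and does not make the senna test wait on the placebo result, so it would serve equally well.

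Under either option, name the powered comparisons, state the same level in the Statistical analysis section, and call senna versus placebo descriptive (about 33% power at 0.025 and 43% at 0.05 with 82 per arm). This is a wording change with no extra patients. Trial status reports 20 enrolled and none through treatment, and the statisticians are to remain blinded, so the rule can still be fixed without knowledge of results.

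### The level for the primary comparisons is 0.025 in the sample size section but 0.05 in the analysis section; Holm's procedure over the two MZRW comparisons settles this at 5% overall and about 80% power against senna

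*Protocol article*

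**What the plan says.** Protocol article, Sample size calculation. The inputs are "Assuming the response rates for TCM, senna and placebo were 40%, 20% and 10%, respectively". The claim drawn from them is that "82 patients per treatment group were deemed sufficient to achieve 80% power in detecting treatment differences". The same section names the underlying calculation as "based on two-sided Chi-square test without continuity correction". It words the level for each comparison as "at a significance level of 0.025 (used to maintain the overall significance level at 5" per cent). Recruitment is then set with an allowance for losses: "assuming a 15% dropout rate, we concluded that a total of 291 patients (97 per arm) would need to be recruited". Under Assignment and blinding, "Block randomization was carried out in 1:1:1 ratio".

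Protocol article, Statistical analysis: "The statistical significance is defined as two-sided *P* value of <0.05". That section gives no level per comparison and no multiplicity rule.

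The number of confirmatory comparisons is not stated. The Background says that MZRW is to be evaluated "by comparing it with the commonly used stimulant laxative senna, as well as with a placebo". Two comparisons fit that aim and fit 0.025 = 0.05/2. The family of two is therefore an inference, though a natural one.

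**The concern.** The two sections give different levels for the same primary endpoint, and someone will have to choose between them. A sponsor who wants consistency could write 0.025 throughout or 0.05 throughout, and each has a cost.

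- **0.025 throughout** holds the overall 5% for two comparisons but restricts the senna comparison to 0.025 even when the placebo comparison has clearly succeeded. On the plan's rates that success is almost certain.
- **0.05 throughout** leaves the senna comparison at the power the plan claims but abandons the overall error rate that the sample size section promises to maintain.

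MZRW versus senna is the new question. The Abstract and the Discussion justify the trial by comparison with a conventional laxative, and placebo has already been studied by the same team. Of the two MZRW comparisons it also has the smaller assumed difference and so the lower power.

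**Working it through.** **Inputs.** Response rates 40%, 20% and 10%; two-sided chi-square without continuity correction; 80% power; 82 per arm; 15% dropout; 97 per arm, 291 in all (Sample size calculation). Allocation 1:1:1 (Assignment and blinding).

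**Formulas**, with p̄ the mean of p₁ and p₂:

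- n = [z(1−α/2)·√(2p̄(1−p̄)) + z(0.80)·√(p₁(1−p₁)+p₂(1−p₂))]² / (p₁−p₂)²
- power = Φ{ [|p₁−p₂|·√n − z(1−α/2)·√(2p̄(1−p̄))] / √(p₁(1−p₁)+p₂(1−p₂)) }

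For 40% against 20%, p̄ = 0.30 and the two square roots are √0.42 = 0.6481 and √0.40 = 0.6325.

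**1. The plan's own sample size.**
- At α = 0.05: [(1.960×0.6481 + 0.8416×0.6325)/0.20]² = 81.2, so 82.
- At α = 0.025: [(2.2414×0.6481 + 0.8416×0.6325)/0.20]² = 98.5, so 99.

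The stated 82 is the two-sided 0.05 answer. It does not reproduce at two-sided 0.025, nor with a continuity correction (109) or with unpooled or arcsine forms (about 95 to 98). The dropout step does reproduce: 82/0.85 = 96.5, so 97, and 3×97 = 291. Starting from 99 it would be 99/0.85 = 116.5, so 117 per arm and 351 in all.

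**2. Power against senna by formula.**
- 82 per arm, 0.025: (0.20×9.055 − 1.4526)/0.6325 = 0.567, power 71.5%.
- 82 per arm, 0.05: (1.8111 − 1.2702)/0.6325 = 0.855, power 80.4%.
- 97 per arm, 0.025: (0.20×9.849 − 1.4526)/0.6325 = 0.818, power 79.3%.
- 97 per arm, 0.05: (1.9698 − 1.2702)/0.6325 = 1.106, power 86.6%.

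**3. Power against placebo.** For 40% against 10% at 0.025 with 82 per arm, p̄ = 0.25 and the power is 99.0%. Holm's first step is therefore almost always passed, and senna is then tested at 0.05.

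**4. Fixed 0.025 against Holm.** Three independent binomial arms, 1,000,000 simulated trials per scenario. Holm tests the smaller P at 0.025 and, if that is significant, the other at 0.05.

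| Scenario | Power against senna, fixed 0.025 | Power against senna, Holm |
|---|---|---|
| 82 per arm, 40/20/10% | 72.3% | 80.6% |
| 97 per arm, 40/20/10% | 80.1% | 87.0% |
| 97 per arm, 15% dropouts counted as non-responders (34/17/8.5%) | about 70% | about 79% |

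The third row multiplies each rate by 0.85. It is an assumption that marks the unfavourable end of the range. The second row assumes that dropouts respond at the full rates.

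**5. Overall error.** With all three rates at 20% and 82 per arm, the chance of at least one false claim is 4.7% under both rules. With MZRW and senna both at 40% and placebo at 10%, Holm falsely separates MZRW from senna in 4.7%. Testing both comparisons at an unadjusted 0.05 allows up to 2×0.05 = 10%; the simulated figure with all rates at 20% is about 9%.

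**6. Sensitivity.** If placebo responds at 20%, the same as senna, Holm still gives 77.4% against 72.3% at 82 per arm. If senna versus placebo were a third confirmatory comparison, 0.025 each would no longer guarantee 5%, and Holm over three would give about 76% for MZRW versus senna at 82 per arm.

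**The case against.** The strongest reply is that the document never fixes a 0.025 test for the analysis. The figure appears only in the sample size section, Bonferroni is not named, and sizing at the strictest level is compatible with a step-down analysis set out in a statistical analysis plan that is not shown. This stands in part. A reader might infer that the plan has adopted a fixed split and so throws away 8 points of power. The article does not support that, because its analysis section says 0.05. The loss follows only if the conflict is settled as a fixed 0.025. What remains is that the article states two incompatible levels, which is a contradiction on the page and not a detail deferred.

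A second reply is that the shortfall from 80% comes mainly from the sample size and not from the procedure: 99 evaluable per arm would give 80.2% at fixed 0.025. That is right. A reader might also infer that the choice of procedure decides whether 80% is reached with the planned patients. It does not in every case: with all 97 per arm at the full rates, the fixed split already gives about 80%, and with dropouts as non-responders even Holm gives about 79%.

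Third, Holm is not free of cost. It rejects everything the fixed split rejects, but matching simultaneous confidence intervals are simpler under the fixed split. Nor is it the only option: testing placebo first and then senna, each at 0.05, gives nearly the same power against senna on these rates.

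**Conclusion.** The concern holds as a conflict between two sections for which a better resolution exists than either stated level. Settled as fixed 0.025, MZRW versus senna has about 72% power at 82 evaluable per arm, not the stated 80%. Settled as unadjusted 0.05, the overall 5% is not protected. Holm over the two MZRW comparisons holds 5% and gives about 80% at 82 per arm, a gain of about 8 points; at 97 per arm the gain is about 7 points (80% to 87%). Holm thus restores roughly the power the plan already claims at 82 and does not exceed it.

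This rests on the plan's rates of 40/20/10%, on a family of two inferred from the Background and from 0.05/2, and, for the 97-per-arm figures, on dropouts responding at the full rates. It is a matter of efficiency and consistency. A fixed 0.025 would be a valid test for two comparisons.

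**What to change.** In both Sample size calculation and Statistical analysis, state one rule, for example: *The two primary comparisons, MZRW with placebo and MZRW with senna, are tested by Holm's procedure at an overall two-sided 5%: the smaller P value at 0.025 and, if it is significant, the other at 0.05. Senna versus placebo is outside this confirmatory family.*

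Restate the power for MZRW versus senna as about 80% at 82 evaluable per arm. Quote about 87% at 97 per arm only with the note that it assumes dropouts respond at the full rates, and give about 79% for the case where the 15% count as non-responders. State how simultaneous confidence intervals will be reported.

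The cost is a few sentences, with no extra patients and no new data. Trial status reports 20 enrolled and none through treatment, and the statisticians are to stay blinded until the study is complete, so the rule can be set before any unblinded result is seen.
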